### Multimodal neuroimaging acquisitions and analyses

Structural T1-weighted MRI images will be acquired using a three-dimensional magnetization-prepared rapid gradient-echo (3D MPRAGE) sequence with the following parameters: repetition time (TR)/echo time (TE)/inversion time (TI) = 240/2.14/100 ms, flip angle = 8 degrees, field of view (FOV) = 224 x 224 mm, voxel size = 0.7 mm isotropic, bandwidth = 210 Hz/pixel, integrated parallel acquisition techniques (iPAT) = 2, and an acquisition time of 7 minutes and 40 seconds. T2-weighted images will be acquired using a 3D T2 sampling perfection with application-optimized contrasts using different flip angle evolutions (T2-SPACE) sequence, with parameters: TR/TE = 320/565 ms, variable flip angle, FOV = 224 x 224 mm, voxel size = 0.7 mm isotropic, bandwidth = 755 Hz/pixel, iPAT = 2, and an acquisition time of 8 minutes and 24 seconds. The total duration for structural imaging acquisition will be 16 minutes and 4 seconds. Resting-state functional MRI (fMRI) images will be acquired with the following specifications: TR/TE = 720/33.1 ms, flip angle = 52 degrees, FOV = 208 x 180 mm, matrix size = 104 x 90, slice thickness = 2.0 mm, 72 slices, 2.0 mm isotropic voxels, multiband factor = 8, echo spacing = 0.58 ms, and bandwidth = 229 Hz/pixel. The acquisition of resting-state functional images will require 14 minutes and 33 seconds.

A 48-channel functional near-infrared spectroscopy (fNIRS) device (NirScan model from Danyang Huichuang Medical Equipment Co. Ltd in China) will be employed in this study. The fNIRS data will be collected during the administration of The Chinese version of the Verbal Fluency Test (VFT) serves to evaluate verbal fluency, working memory, verbal recall, attention, and retrieval capabilities. The VFT task is structured into three distinct phases: a 30-second pre-task baseline period, a 60-second task period, and a 70-second post-task period. The baseline phase is characterized by the absence of VFT task performance. During the 30-second pre-task baseline phase, participants are instructed to count repeatedly from one to five until the commencement of the task period. In the subsequent 60-second VFT task period, participants are required to generate as many phrases as possible using simple words such as “white,” “north,” and “big.” Following the completion of the phrase generation task, participants are instructed to resume counting from one to five repeatedly throughout the 70-second post-task period. Fifteen light source probes and sixteen light detector probes will be positioned on the bilateral frontotemporal cortex, with a distance of 3 cm maintained between each light source and detector probe. In accordance with the 10/20 electrode placement system, the central probe will be positioned at FPz, while the lower boundary of the probe array will extend from Fp1 to Fp2. Hemodynamic changes will be assessed through measurements of oxyhemoglobin, deoxyhemoglobin, and total hemoglobin. Resting-state and task-state fNIRS data acquisitions will be performed for all participants in this study. The raw fNIRS data will be preprocessed utilizing the MATLAB Home 3 toolkit. Five statistical metrics—mean, variance, skewness, kurtosis, and peak value—will be calculated for changes in oxy-Hb signals, based on the spatial average across all 48 channels. This methodology will generate a total of 240 independent features for each subject.

The resting-state EEG data were recorded utilizing a PN-NET multichannel electroencephalogram device with 64 scalp electrodes, 1 reference electrode on the nose tip, and 2 electro-ocular electrodes positioned at the right eye corner and beneath the left eye. Data collection transpired in a tranquil examination room by a consistent researcher. Subjects were instructed to maintain stillness, wakefulness, and relaxation, minimize bodily and ocular movements, and abstain from specific tasks. Electrode impedance was maintained below 5 kΩ to ensure data fidelity during collection. A sampling rate of 1,024 Hz was employed, capturing EEG data with closed eyes over a 5-minute interval.

### Biological assessment

Participants will undergo a fasting anterior elbow vein puncture to collect a 5 ml blood sample, which will be transferred to an anticoagulant tube and centrifuged at 300 rpm for 10 minutes. The supernatant and sedimented blood cells will be separately transferred into two Eppendorf tubes. Subsequently, the centrifuge tube will be placed in a freezing centrifuge for further centrifugation. The supernatant will be aspirated, and its protein concentration will be quantified using the BCA kit. Subsequently, equal volumes of samples and molecular weight standards will be subjected to Tris-SDS-PAGE electrophoresis, followed by transfer onto a PVDF membrane. The membrane will be incubated in a 5% skimmed milk solution for blocking for a duration of 2 hours. After a washing step, primary antibodies specific to BDNF and β-actin, diluted at a ratio of 1:500, will be applied and incubated overnight at 4°C. Thereafter, secondary antibodies, also diluted at a ratio of 1:500, will be introduced and incubated at room temperature for 2 hours. The PVDF membrane containing the target protein will then be immersed in a developing solution for analysis using a chemiluminescence imaging analyzer. The exposure time will be adjusted based on the protein’s abundance, and the expression levels of BDNF will be quantitatively assessed using ImageJ software.

For the assessment of secondary outcomes, this study employed the Repeatable Battery for the Assessment of Neuropsychological Status (RBANS) and the Wisconsin Card Sorting Test (WCST) to evaluate global and executive functions. Simultaneously, the Facial Emotion Perception Test (FEPT) and the Voice Emotion Perception Test (VEPT) were utilized to assess emotion perception abilities within the domain of social cognition. The severity of clinical symptoms and overall changes were quantified using the Positive and Negative Syndrome Scale (PANSS) and the Brief Psychiatric Rating Scale (BPRS). Furthermore, improvements in social functioning and quality of life were evaluated using the Social Disability Screening Schedule (SDSS) and the Schizophrenia Quality of Life Scale (SQLS). The RBANS comprises five components: immediate memory, visuospatial skills, language, attention, and delayed memory. Its notable features include ease of administration, brief administration time, and robust reliability and validity. The RBANS is effective for detecting cognitive impairment and can also be used to assess changes in cognitive function following treatment or intervention (50). The WCST is a widely utilized standardized tool in neuropsychological research and clinical cognitive assessment, primarily crafted to assess cognitive flexibility and abstract thinking within executive functions. Participants must discern classification rules based on evolving feedback (e.g., color, shape, or number) and adapt their strategies accordingly. This assessment effectively mirrors the operation of the prefrontal cortex and is frequently employed to pinpoint executive function impairments linked to psychiatric disorders, brain injuries, and ageing (51). The FEPT is predominantly employed to gauge an individual’s capacity to perceive and comprehend the emotions conveyed in the facial expressions of others. This evaluation presents a sequence of standardized facial expression images (e.g., happiness, sadness, anger, fear, etc.), requiring participants to recognize the type or intensity of emotion (52). The VEPT is employed to assess an individual’s ability to perceive emotional nuances in others’ voices. Participants listen to voice samples (neutral or expressing emotions like joy, sadness, anger, etc.) and must identify the specific emotion conveyed (53). The BPRS is utilized to gauge the intensity of psychiatric symptoms, with higher scores indicating more pronounced symptom severity (54). The PANSS is a widely used standardized tool in psychiatric clinical and research settings, primarily crafted to evaluate symptom severity in individuals with schizophrenia (55). It consists of the Positive Symptom Scale and the Negative Symptom Scale, each comprising 7 items, alongside a general psychopathology scale with 16 items, totaling 30 items. The SDSS is employed to quantitatively evaluate social functioning impairment in patients, encompassing crucial aspects such as work and social interactions. It is user-friendly and suitable for rehabilitation assessments (56). The SQLS assesses patients’ quality of life using various indicators that mirror their subjective experiences, offering a benchmark for evaluating effectiveness (57).

To explore the underlying mechanisms, the study adopted a multimodal assessment framework. MRI and fNIRS were utilized to investigate changes in brain activity, structure, and functional connectivity. EEG and P300 were employed to capture the neurophysiological dynamics of electrical brain activity. EM served as an objective behavioral-physiological marker of cognitive processing. Additionally, plasma BDNF levels were measured to evaluate the molecular correlates of neurotrophic support and plasticity. This integrated approach aims to elucidate the therapeutic effects of MRI-guided HD-tDCS combined with AE for CIAS and to uncover the neurobiological mechanisms underlying these effects.The procedure for the site visit is outlined in **Table 2**.

**Table 2 T2:** Time schedule of screening, interventions and assessments.

Item	Recruitment	Assessment time point			
		T0	T1	T2	T3
Prescreening for eligibility, consenting, and clinical interview							
Recruitment					
Eligibility screening	✓				
Informed consent	✓				
Allocation	✓				
Primary outcome assessment					
MCCB		✓	✓	✓	✓
Second outcome assessment					
RBANS		✓	✓	✓	✓
BPRS		✓	✓	✓	✓
SQLS		✓	✓	✓	✓
SDSS		✓	✓	✓	✓
PEPT		✓	✓	✓	✓
VEPT		✓	✓	✓	✓
WCST		✓	✓	✓	✓
Biological assessment					
fNIRS		✓	✓	✓	✓
EEG		✓	✓	✓	✓
EM		✓	✓	✓	✓
P300		✓	✓	✓	✓
MRI		✓	✓	✓	✓
Plasma BDNF		✓	✓	✓	✓
Safety					
ARS			✓	✓	✓

A checkmark (✓) indicates the time point at which each assessment is carried out. ARS, Adverse Reaction Scale; BPRS, Brief Psychiatric Rating Scale; EEG, Electroencephalography; EM, Eye Movements; fNIRS, Functional Near-Infrared Spectroscopy; MCCB, MATRICS Consensus Cognitive Battery; MRI, Magnetic Resonance Imaging; PANSS, Positive and Negative Syndrome Scale; PEPT, Facial Emotion Perception Test; P300, P300 Event-Related Potential; RBANS, Repeatable Battery for the Assessment of Neuropsychological Status; SDSS, Social Dysfunction Screening Scale; SQLS, Schizophrenia Quality of Life Scale; VEPT, Voice Emotion Perception Test; WCST, Wisconsin Card Sorting Test.

T0: baseline, T1: after 2 weeks, T2: after 4 weeks, T3: after 6 months.

### Sample size calculation

We performed the necessary calculations using G*Power software (version 3.1.9.7). Under the following command, test family: F tests; Statistical test: ANOVA: Repeated measures, within-between interaction (58).The research parameters were defined as follows: a Type I error rate of 0.05, a statistical power of 80%, and an effect size of 0.25. Utilizing a repeated measures ANOVA model and considering a potential participant dropout rate of 20%, we determined that the required sample size is 48 patients, with 12 patients assigned to each group. In preliminary studies where prior sample size data are unavailable, a group size of 12 subjects is deemed appropriate. We will justify the rationale for selecting a sample size of 12 per group from three perspectives: feasibility, improved precision in estimating means and variances, and adherence to regulatory requirements (59). This sample size is expected to provide adequate statistical power to address the study objectives.

### Date management

The evaluation of cognitive function and the severity of psychiatric symptoms will be conducted by two psychiatrists, who will remain blinded to the group assignments. All demographic information and scale-related data will be recorded in electronic Case Report Forms (eCRFs) and stored on a designated website. Access to the securely stored eCRFs will be restricted to the project leader and the principal investigator. To maintain confidentiality, anonymization will be implemented during data entry by substituting patients’ actual names with unique identification numbers. The independent data monitoring committee will be established to monitor safety, the occurrence of adverse events, and advise on trial design decisions.

### Statistical methods

The Shapiro-Wilk test will be employed to determine whether the quantitative data conform to a normal distribution. When the quantitative data are normally distributed, they will be described using the mean and standard deviation. If the data deviate from a normal distribution, the median and interquartile range will be utilized for presentation. Categorical data will be presented as counts and percentages. To evaluate differences in baseline characteristics among groups, appropriate statistical tests such as t-tests, nonparametric tests, chi-square tests, Mann-Whitney U tests, or ANOVA will be selected based on the type and distribution of the data. Additionally, Fisher’s exact test or chi-square test will be used to compare adverse reactions between groups.

This study will adhere to the CONSORT guidelines and perform data analysis based on the intention-to-treat principle, ensuring that all participants are evaluated according to their initial randomization assignments. To assess differences in primary and secondary outcomes both between and within groups over time, generalized linear mixed models and repeated-measures ANOVA will be employed as appropriate. A stepwise model selection approach will be implemented to derive a succinct multivariate regression model. Age, gender, and the Defined Daily Dose (DDD) of antipsychotic medications will be included as covariates in all models. The treatment effect will be evaluated using the likelihood ratio test to ascertain whether the coefficients for treatment and the interaction between time and treatment are both zero. To correct for multiple comparisons across time points, the Bonferroni correction method will be applied to adjust the p-values. All statistical analyses will be conducted using SPSS version 20.0, with a significance threshold set at *P* < 0.05 to denote statistical significance. Research framework is illustrated in **Figure 2**.

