This study aims to investigate three principal aspects. The primary objective of this study is to evaluate the efficacy of the combined intervention of HD-tDCS and AE in enhancing cognitive function at the individual level. Additionally, we aim to assess the long-term impact of this intervention over a six-month period, focusing on changes in cognitive function, clinical symptoms-measured by the Positive and Negative Syndrome Scale (PANSS) and Brief Psychiatric Rating Scale (BPRS), social function-measured by Social Disability Screening Schedule (SDSS), and Schizophrenia Quality of Life Scale (SQLS). Furthermore, the study seeks to elucidate the biological mechanisms of MRI-guided HD-tDCS and AE from a multi-dimensional perspective. By evaluating the feasibility and safety of this precision approach, the study aims to provide biological insights into individualized treatment strategies for CIAS.

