### Harms

To evaluate the safety and potential adverse effects of HD-tDCS, this study will thoroughly investigate both severe and mild adverse events. All participants will be required to complete the HD-tDCS Adverse Reaction Scale (ARS), which encompasses common side effects such as tingling, mild redness, itching, and discomfort at the stimulation site. Participants will rate their adverse reactions on a scale from 0 to 5, with all occurrences documented in the CRFs. The HD-tDCS equipment will be operated by trained therapists proficient in its use, aiming to minimize the risk of participants encountering any significant health hazards or adverse effects. In the event of a severe adverse reaction, the participant will be withdrawn from the study, and the incident will be promptly reported to the ethics committee.

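### Adverse reactions are graded 0 to 5, but the only tests named for them ignore severity order; add an ordinal comparison with an interval

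*Protocol article*

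**What the plan says.** The Harms section of the protocol article has every participant complete an HD-tDCS Adverse Reaction Scale (ARS) covering stimulation-site effects such as tingling, redness, itching and discomfort, which it describes as common. On the grading it says: "Participants will rate their adverse reactions on a scale from 0 to 5, with all occurrences documented in the CRFs". Table 2 schedules the scale at T1, T2 and T3.

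Statistical methods names one approach for these data: Fisher's "exact test or chi-square test will be used to compare adverse reactions between groups". It does not say whether that means occurrence or grade, and it names no pair of groups. The longitudinal models are reserved for other endpoints: "To assess differences in primary and secondary outcomes both between and within groups over time, generalized linear mixed models and repeated-measures ANOVA" are named for those, and adverse reactions are not listed among the primary or secondary outcomes. The same section already includes the Mann-Whitney U test, but for baseline characteristics.

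Safety is among the stated aims at the end of the Background: "By evaluating the feasibility and safety of this precision approach". Only Group 1 (stimulation plus exercise) and Group 2 (stimulation alone) receive current. There are 12 patients per group and an assumed dropout of 20%.

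**The concern.** A six-level ordered rating is collected, and the only tests named for it make no use of order. To apply them, the grades must be reduced to reaction or no reaction, or treated as six unordered categories.

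Reduced to yes/no, the comparison meets a ceiling if nearly every stimulated patient feels something: two arms with similar incidence can differ clearly in severity and still look alike. Treated as six categories, 24 patients spread over 2 x 6 = 12 cells average 2 per cell, so the table is sparse as well as unordered.

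At stake is what the trial can say about whether adding exercise changes the severity of stimulation reactions. The grades that could inform this are collected, but no named analysis uses their order.

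**Working it through.** **The plan's own figure.** The only sample-size calculation concerns the repeated-measures outcome: "a Type I error rate of 0.05, a statistical power of 80%, and an effect size of 0.25". With four groups, four time points and an unstated correlation assumed to be 0.5, the noncentral F calculation gives N = 36, or 9 per group (power 0.825). Then 9 / 0.8 = 11.25, rounded up to 12, and 4 x 12 = 48, which matches. No figure is given for adverse reactions.

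**Inputs for the check.** From the article: grades 0 to 5, 12 per arm (about 10 after 20% dropout), threshold 0.05. Assumed: two-sided testing, and Group 2 worst-grade distributions (grades 0 to 5) of
- 85% reacting: .15, .30, .25, .15, .10, .05
- 70%: .30, .30, .20, .10, .07, .03
- 50%: .50, .20, .14, .08, .05, .03
- 30%: .70, .12, .08, .05, .03, .02

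**Shift.** Group 1 follows a proportional-odds shift: at each cut, odds(grade ≤ k) in Group 1 = odds(grade ≤ k) in Group 2 / OR. Example, 70% reacting and OR 5: the odds of no reaction are 0.30/0.70 = 0.429; 0.429/5 = 0.0857; 0.0857/1.0857 = 0.079, so 92% react in Group 1. The mean grade rises by about 0.75 to 0.90 at OR 3 and 1.2 to 1.4 at OR 5.

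**Why yes/no saturates.** Suppose all 12 patients in Group 1 react. If 8 of 12 react in Group 2, Fisher's two-sided p = 2 x C(12,4)/C(24,4) = 990/10626 = 0.093. If 7 react, p = 2 x C(12,5)/C(24,5) = 1584/42504 = 0.037. So at most 7 may react in Group 2. At 85% incidence the expected number is 0.85 x 12 = 10.2.

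**Power (%), 12 per arm.** The 2x2 tests are computed by full enumeration (chi-square without continuity correction). The six-category chi-square and the tie-corrected Mann-Whitney test use 20,000 simulated trials per row.

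| Group 2 reacting | OR | Fisher yes/no | Chi-square yes/no | Chi-square, 6 categories | Rank test | Rank-test gain over named tests (points) |
|---|---|---|---|---|---|---|
| 85% | 3 | 1.2 | 4.9 | 10.6 | 30.5 | 19.9 to 29.3 |
| 70% | 3 | 7.2 | 15.6 | 11.1 | 30.4 | 14.8 to 23.2 |
| 50% | 3 | 14.3 | 26.4 | 11.2 | 30.2 | 3.8 to 19.0 |
| 30% | 3 | 15.9 | 28.8 | 8.5 | 26.4 | -2.4 to 17.9 |
| 85% | 5 | 1.6 | 6.2 | 23.5 | 56.1 | 32.6 to 54.5 |
| 70% | 5 | 12.0 | 24.2 | 23.9 | 56.3 | 32.1 to 44.3 |
| 50% | 5 | 26.8 | 42.9 | 24.6 | 55.5 | 12.6 to 30.9 |
| 30% | 5 | 35.3 | 52.6 | 20.8 | 51.6 | -1.0 to 30.8 |

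With no true difference, the rank test rejects in 4.7 to 4.9% of trials; the 2x2 chi-square rejects in 2.9 to 6.4%. With 10 per arm, the gain at 70 to 85% reacting runs from 13.9 points (25.3 against 11.4) to 47.8 points (48.5 against 0.7).

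**Other assumed distributions, 12 per arm.**
- 60% reacting, OR 4: rank 47%; Fisher yes/no 17%, chi-square yes/no 30%, six-category chi-square 18%.
- 95% reacting, OR 10: rank 84%; both yes/no tests about 0%; six-category chi-square 52%.
- Difference in incidence only (20% against 70%): rank 76%, chi-square 76%, Fisher 60%.
- Equal incidence with grades spread differently: six-category chi-square 31% and 65%, rank 20% and 58%.

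**The case against.** The strongest reply is that the Harms sentence also has every occurrence recorded, and Fisher's exact or chi-square is the standard comparison of occurrence. On that reading the named tests fit their data, and how a safety scale is summarised can be left to an analysis plan that is not shown. The first part stands: the tests are right for occurrence and should stay. The second stands only in part. The article does fix a method for adverse reactions, and that method leaves the order of the grades unused.

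Three stronger readings are tempting, and the documents do not support them.
- A reader might infer a definite loss of power. The article gives no incidence, grade distribution or expected shift. With 30% reacting, the 2x2 chi-square does as well as the rank test (28.8% against 26.4%, and 52.6% against 51.6%). Where arms differ in spread rather than level, the six-category test can be stronger.
- A reader might infer that Group 1 versus Group 2 is the planned tolerability test. The article says only that groups are compared, and there are four. The contrast is natural because these are the two stimulated arms, but it is not designated.
- A reader might infer that the trial will declare the combination equally tolerable on a non-significant result. Nothing in the article says so, no safety comparison is powered, and the limitations concede that the sample is small.

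It is also fair that an ordinal test does not rescue the comparison: its power in the main table is 26 to 56%. Testing each item separately would add multiplicity that these calculations do not cover.

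**Conclusion.** The point holds as a modest improvement to a stated method. The article collects 0 to 5 severity from every participant and names only tests that ignore order. That matters most where reactions are frequent, which is how the Harms section describes them. At 70 to 85% reacting, with odds ratio 3 to 5 and 12 per arm, a rank test gains roughly 15 to 50 points over the named tests (14.8 to 54.5 in the table). At 30% reacting, or 50% at the smaller shift, it gains little or nothing over a 2x2 chi-square (-2.4 to 3.8 points).

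This is a range of scenarios and not an estimate for the trial. It rests on assumed grade distributions, a proportional-odds shift, one worst grade per participant and two-sided testing. Because power stays low with any test at this size, the estimate and its interval must carry the conclusion.

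**What to change.** In Statistical methods, keep Fisher's exact or chi-square for the occurrence of reactions and of serious events in all groups, and add wording such as:

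*ARS severity, taken as each participant's worst grade (0 to 5) overall, will be compared on the ordinal scale by the exact Mann-Whitney test or a proportional-odds model. The main contrast is Group 1 versus Group 2, the two stimulated arms. The result will be reported as an estimate (the common odds ratio, or the probability that a Group 1 grade exceeds a Group 2 grade) with its 95% confidence interval. Item-level results are descriptive. A non-significant result will not be interpreted as equal tolerability.*

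One of the two methods should be chosen before unblinding. The cost is a sentence or two: the grades are already collected, the Mann-Whitney test is already in the plan, and no patients or visits are added. The downside is one additional safety analysis that remains low-powered. A single overall worst grade avoids a family of item-level tests, but hides which symptom drives a difference; the descriptive item table covers that.

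### The primary analysis is not fixed to one model, and its likelihood ratio test, read in the usual way, has a type I error of about 7–13% at 12 per arm instead of 5%

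*Protocol article*

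**What the plan says.** All of the following stands in the Statistical methods section of the protocol article.

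- Primary and secondary outcomes: "generalized linear mixed models and repeated-measures ANOVA will be employed as appropriate". No criterion for the choice is given.
- Model building: "A stepwise model selection approach will be implemented to derive a succinct multivariate regression model". Neither candidate terms nor an entry or removal rule is named.
- Age, gender and the antipsychotic defined daily dose (DDD) "will be included as covariates in all models".
- Decision test: "The treatment effect will be evaluated using the likelihood ratio test", applied jointly to the treatment and the time-by-treatment coefficients, at P < 0.05. The reference distribution is not named. Bonferroni is applied across time points only.
- Population: the trial will "perform data analysis based on the intention-to-treat principle".

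The Sample size calculation section plans 48 patients, 12 per arm, on a different test: the within-between interaction F test of a repeated-measures ANOVA, with 20% dropout.

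**The concern.** The article prescribes a route to the primary result that has several branches and lets outcome data choose among them.

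- Stepwise selection shapes the model on the outcome, and the final p-value takes no account of that.
- The two permitted model families differ in how they treat missed visits, covariance and the reference distribution, so they can disagree on the same data.
- A likelihood ratio test on many parameters relies on a large-sample approximation, which is poor with 12 patients per arm.
- The test that was powered is not the test that decides.

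At stake is whether a significant primary result carries the 5% false-positive risk that the article states.

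**Working it through.** **1. The plan's own figure.** The inputs are "a Type I error rate of 0.05, a statistical power of 80%, and an effect size of 0.25", four arms, four visits and 20% dropout. The article gives neither the within-subject correlation ρ nor the sphericity factor ε, so ρ = 0.5 and ε = 1 are assumed (the G*Power defaults).

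- Noncentrality λ = f² × N × m/(1 − ρ); df1 = (4 − 1)(4 − 1) = 9; df2 = (N − 4) × 3.
- At N = 36: λ = 0.0625 × 36 × 4/0.5 = 18 and df2 = 96, giving power of about 0.825. The smallest N reaching 80% is 35, which rounds to 36, or 9 per arm.
- Dropout: 9/0.8 = 11.25, so 12 per arm and 48 in total.

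The stated 48 is reproduced, for the ANOVA interaction test.

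**2. Degrees of freedom of the deciding test.** Treatment 4 − 1 = 3, plus interaction 3 × 3 = 9, gives 12. If only the three post-baseline visits are responses, it is 3 + 6 = 9.

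**3. Why chi-square is too generous here.** With complete data, an unstructured covariance and visit-specific covariate effects, the statistic is N × ln(|S0|/|S1|). S0 and S1 are the residual cross-product matrices without and with treatment. Bartlett's small-sample version replaces N by ν − (4 − 3 + 1)/2 = ν − 1, where ν = N − 4 − (number of covariates). The 5% critical value of chi-square on 12 df is 21.03.

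| Per arm | Covariates | N | ν − 1 | 21.03 × (ν − 1)/N | Chi-square(12) tail |
|---|---|---|---|---|---|
| 12 | 0 | 48 | 43 | 18.84 | 9.3% |
| 12 | 3 | 48 | 40 | 17.52 | 13.1% |
| 10 | 0 | 40 | 35 | 18.40 | 10.4% |
| 10 | 3 | 40 | 32 | 16.82 | 15.6% |

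With three covariates at N = 48, the unscaled statistic is 48/40 = 1.2 times too large.

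**4. Null simulation of the likelihood ratio test** (four visits, nominal 5%):

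| Covariance and covariates | 12 per arm | 10 per arm |
|---|---|---|
| Compound symmetry, none | 7.3% | 7.6% |
| Random intercept, three | 8.5–9.3% | 9.0–10.0% |
| Unstructured, none | 9.2% | 10.4–10.6% |
| Unstructured, three (time-constant) | 11.0% | 11.8% |
| Unstructured, three (visit-specific) | 13.0–13.5% | 15.2–15.7% |

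With three visits and three covariates the range is 8.0–11.2% at 12 per arm and 8.7–13.3% at 10. In the last row of the table, Bartlett scaling brings 13.5% to 5.4% (12 per arm) and 15.4% to 5.0% (10 per arm). The reference distribution is therefore the cause.

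**5. Open model choice.** Taking the smaller p of the random-intercept likelihood ratio test and the ANOVA interaction F gives 9.2–10.3% at N = 48. In the matching four-visit compound-symmetry case this adds little: 8.5% becomes 9.4%. Taking the smallest p over both likelihood ratio tests, the interaction F and the group F gives 14.8–17.9%, an outer bound.

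**6. Stepwise selection of extra covariates only** (forward, p < 0.05): 5.7–6.7% with 5 candidates and 7.0–8.5% with 10, against about 5% without selection. The candidate numbers are assumptions.

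**7. Missed visits.** 48 × 0.8 = 38.4, so about 38 complete cases, 9 to 10 per arm.

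**The case against.** The strongest reply is that the article says only that a likelihood ratio test will be used. Reference distribution, covariance and small-sample correction are commonly left to an analysis plan, which is not shown. This stands as a limit on the size of the inflation, and the figures are therefore conditional. It does not answer the stepwise sentence or the open model choice, which the article states outright.

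It can also be said that the ANOVA F test holds its level (5.1% and 4.5% at 12 and 10 per arm under compound symmetry), that dropout was allowed for in the 48, and that the Blinding section keeps analysts on coded groups. All three are fair. But coded analysts still see whether a result is significant, and an allowance for dropout in the sample size does not put the dropped patients back into the analysis.

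Three stronger readings are tempting and are not supported:

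- **That stepwise selection contradicts the fixed covariates.** Three forced-in covariates can coexist with selection among others. The text is unclear here, but not contradictory.
- **That the plan as a whole breaks intention-to-treat.** Neither stepwise selection nor a likelihood ratio test changes who is analysed or in which arm. The tension arises only if repeated-measures ANOVA is run on complete cases, and the article does not say that it will be.
- **That individual treatment terms are screened stepwise, with very large inflation.** The article tests treatment and interaction jointly, so the natural reading keeps both in the model. Even with interaction and then main effect in the pool, two independent tests give 1 − 0.95² = 9.75%.

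The absence of baseline MCCB from the covariates is not an error either. T0 is one of the repeated measures, so the interaction already captures change from baseline.

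**Conclusion.** The point holds in this form: the article does not fix one primary analysis, and the test it names has a type I error above 5% at this sample size on its ordinary reading. The size is about 7–13% at 12 per arm and about 8–16% at 10 per arm. Selection of covariates alone gives about 6–8.5%.

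These figures assume normal data, complete visits within each simulated arm size, a chi-square reference, and within-subject correlations of 0.6 to 0.7. The low end is compound symmetry without covariates. The high end is an unstructured covariance with three covariates whose effects vary by visit. The conflict with intention-to-treat is confined to a complete-case ANOVA. Because this governs the primary efficacy conclusion and recruitment has begun, it should be settled before any outcome data are examined.

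**What to change.** 1. Delete the stepwise sentence and the repeated-measures ANOVA alternative.
2. Name one REML linear mixed model on all randomised patients, using every observed visit: arm, visit, arm × visit, age, sex and baseline DDD. Specify an unstructured covariance and name the fallback structure to be used if it does not converge.
3. State the role of T0 MCCB. Either T0 stays among the responses, or it becomes a covariate and only T1–T3 are responses. It cannot be both.
4. Replace the uncorrected likelihood ratio test with F or t tests on Satterthwaite degrees of freedom. One caution: the calculations above show that Bartlett scaling restores the level, but they do not cover the Satterthwaite F. Single-contrast t tests are safe, but a joint F over many contrasts with an unstructured covariance can stay slightly above nominal. If the joint test remains decisive, check its level by simulation beforehand or use the scaled statistic.

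The cost is analysis wording only, and the model runs in the software already planned. The downside is slightly larger, correct p-values.
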